## Abstract

**Background:**

It is reported that nursing is one of the most vulnerable jobs for developing depression. While they may not be clinically diagnosed as depressed, nurses often suffer from depression and anxiety symptoms, which can lead to a low level of patient care. However, there is no rigorous evidence base for determining an effective prevention strategy for these symptoms in nurses. After reviewing previous literature, we chose a strategy of treatment with omega-3 fatty acids and a mindfulness-based stress management program for this purpose. We aim to explore the effectiveness of these intervention options for junior nurses working in hospital wards in Japan.

**Methods/Design:**

A factorial-design multi-center randomized trial is currently being conducted. A total of 120 nurses without a managerial position, who work for general hospitals and gave informed consent, have been randomly allocated to a stress management program or psychoeducation using a leaflet, and to omega-3 fatty acids or identical placebo pills. The stress management program has been developed according to mindfulness cognitive therapy and consists of four 30-minute individual sessions conducted using a detailed manual. These sessions are conducted by nurses with a managerial position. Participants allocated to the omega-3 fatty acid groups are provided with 1,200 mg/day of eicosapentaenoic acid and 600 mg/day of docosahexaenoic acid for 90 days.

The primary outcome is the change in the total score of the Hospital Anxiety and Depression Scale (HADS), determined by a blinded rater via the telephone at week 26. Secondary outcomes include the change in HADS score at 13 and 52 weeks; presence of a major depressive episode; severity of depression, anxiety, insomnia, burnout, and presenteeism; utility scores and adverse events at 13, 26 and 52 weeks.

**Discussion:**

An effective preventive intervention may not only lead to the maintenance of a healthy mental state in nurses, but also to better quality of care for inpatients. This paper outlines the background and methods of a randomized trial that evaluates the possible additive value of omega-3 fatty acids and a mindfulness-based stress management program for reducing depression in nurses.

**Trial registration:**

Clinicaltrials.gov: NCT02151162 (registered on 27 May 2014).

## Background

Hospital nurses are vulnerable to psychological stress and mental disorders [1]. In early reports, the suicide rate of female nurses was significantly higher than that of average workers, and their life expectancy at the age of 45 years was 26.9 years, which is only one year more than that of miners [2]. In a cross-sectional survey conducted in Cyprus, 65% of nurses reported that their job was stressful, and the prevalence of fatigue was higher in females (93%) than in males (88%) [3].

Consequently, nursing is highly associated with depression. The prevalence of depressive symptoms above a clinical cut-off among hospital-employed nurses is 18% in the United States [4]. Nurses with depression are not only likely to suffer personally, but their illness may also have an impact on the quality of care for patients, through an increase in presenteeism. In terms of the monetary burden of patient care, the costs due to increased falls and medication errors that are caused by presenteeism are estimated at 1,346 USD per nurse annually [5].

A systematic review conducted on psychological distress among hospital nurses in the United States reported that emotional fatigue and burnout in nurses is associated with lack of support from senior management in the form of safety programs, and support from supervisors, respectively [6]. Less-experienced junior nurses need support from senior colleagues and require interventions to empower resilience in order to alleviate their psychological distress.

When considering the possible options for intervention in depression, pharmacological treatments can be discounted because they are not useful as a preventive intervention due to their adverse side effects. Instead, lifestyle interventions, such as exercise and diet, are highly likely to be easily implemented and are promising options. With regard to exercise, according to a systematic review of randomized controlled trials (RCTs), depressive symptoms among patients with a chronic illness and functioning problems were reduced [7]; however, rigorous evidence has not supported exercise as a preventive measure for depression and anxiety symptoms among the elderly [8] or children and young people [9]. In addition, intensive exercise may not be feasible due to the busy schedule of nurses working in hospitals. In contrast, the most feasible interventions may be diet. Omega-3 polyunsaturated fatty acids (PUFAs), in particular eicosapentaenoic acid (EPA) and docosahexaenoic acid (DHA), have been most frequently evaluated for their effects on depression and anxiety disorders. Many previous systematic reviews that have accumulated data from RCTs have been published; however, there are some reviews that show a positive effect of omega-3 PUFAs [10] and others that do not [11]. In addition, these reviews did not focus on preventative interventions.

In a recently published comprehensive meta-analysis [12], omega-3 PUFAs were effective in patients with a diagnosis of major depressive disorder, but not effective at preventing depression in healthy subjects. In this analysis, three parallel design RCTs for the prevention of depression in healthy subjects were assessed, with a follow-up duration of over three months. The studies employed a daily dose of 1.093 g EPA and 0.226 g DHA [13], 3.0 g EPA and 0.6 g DHA [14] or 3.0 g EPA and 0.6 g DHA [15]. However, a high daily EPA dose of between 1,000 and 1,500 mg/d with a ratio of 2:1 DHA is argued as optimal for affective disorders [16]. Based on the current evidence for omega-3 PUFAs as a preventive tool for anxiety and depressive symptoms, we believe that methodologically rigorous trials employing optimal doses of EPA and DHA are still needed.

On the other hand, psychological interventions, such as stress management, problem solving and support should be considered as possible interventions in workplace settings because of their feasibility and accessibility. A Cochrane review [17] has revealed that a psychological intervention to alleviate stress among workers in the workplace can be efficacious according to several small RCTs; however, this review concluded that the methodological quality of these trials was not sufficient, and further methodologically sound trials with a larger sample size are needed to reach firm conclusions.

Among the various types of psychotherapy, mindfulness-based cognitive therapy and meditation have been given particular attention by both clinicians and researchers. In a systematic review, mindfulness meditation programs have shown moderate evidence of improvements in depression, with an effect size of 0.30 (95% confidence interval (CI): 0.00 to 0.59) at post-treatment), when compared with nonspecific active controls [18]; however, the review focused on a clinical sample and therefore was not able to conclude any preventive effects of the psychotherapy. To the best of our knowledge, there has been no systematic review focusing on the prevention of depression and anxiety symptoms in the workplace. Although the efficacy of mindfulness-based cognitive therapy in nurses has been examined in a previous RCT [19], the trial included only a small number of participants and no firm conclusions could be drawn. For this reason, a conclusive RCT is necessary to establish evidence of an effective psychological intervention that can help to maintain a healthy mental state in hospital nurses.

Hence, the present study aims to conduct a methodologically rigorous factorial-design trial with 1:1:1:1 allocation to explore the effectiveness of omega-3 PUFAs, and a mindfulness-based stress management program for maintaining a healthy mental state in hospital nurses.

## Methods/Design

### Trial design

A parallel-arms factorial-design RCT with a 52-week follow-up period has been planned. Participants will be randomly allocated to one of the four intervention arms: 1) mindfulness-based stress management program plus omega-3 PUFAs; 2) mindfulness-based stress management program plus placebo; 3) psychoeducation leaflet plus omega-3 PUFAs and 4) psychoeducation leaflet plus placebo. A total of 30 participants will be allocated to each arm. These interventions will terminate within three months from the registration of the participant. The primary outcome will be the depression and anxiety severity at 26 weeks (rated blindly), assessed using the 14-item Hospital Anxiety and Depression Scale (HADS). After each assessment, an assessor will guess which group the participant has been assigned to, making it possible to examine if the blinding is successful.

### Inclusion criteria

The inclusion criteria for participants are as follows:Aged between 20 and 59 years at entry to the study and of female gender. We will limit participants to the female gender because a previous study investigating the prevention of post-traumatic stress among emergency workers has demonstrated that omega-3 fatty acids are effective in females but not males [20]. This is the first study to examine the effectiveness of omega-3 fatty acids among nurses, therefore we have decided to focus on females to maximize the benefit.Nurses who work in inpatient wards at four general hospitals in the Tama region of Japan, including the National Center of Neurology and Psychiatry Hospital, National Disaster Medical Center, Tokyo Metropolitan Tama Medical Center and Tama-Hokubu Medical Center.Those who are mainly engaged in caring for patients, but not in administrative responsibilities. Thus, head nurses in wards and senior nurses who are mainly engaged in supporting administrative work of the head nurses are excluded. A previous study has shown that senior nurses have less burnout than junior nurses [21], and senior nurses are engaged in administrative work in the hospitals included in our study.Those who have given written informed consent to participate in the study.

### Exclusion criteria

The exclusion criteria are as follows:Plans to take sick leave, leave for other reasons or retirement within 26 weeks from entry to the study;Already engaging in structured psychotherapy (such as cognitive behavioral therapy, interpersonal therapy or brief psychodynamic therapy) at entry;Seeing a physician regularly for the treatment of any mood or anxiety disorders at entry;Taking antidepressants, mood stabilizers, anticonvulsants or antipsychotics at entry;Any history of taking nutrient supplements, including omega-3 fatty acids, for four or more weeks within 52 weeks from entry;Clinical depression, based on a total score of 11 or more on the HADS - Depression Subscale [22] and 15 or more on the Primary Health Care Questionnaire [23];Consumption of fish as the main course of a meal four or more times per a week;Taking anticoagulant drugs at entry or history of stroke or myocardial infarction orJudged ineligible by a clinical research coordinator (CRC) for any reason.

### Procedures

Information about the study will be presented to the head of the hospital, the director of the nursing service department and head nurses in explanatory meetings at the recruiting hospitals. Leaflets with information about the study will be distributed to nurses in hospital wards and interested nurses will be contacted by a CRC. Each nurse will input her data, except the HADS criterion, into an electronic data capturing (EDC) system via the internet, with some assistance by the CRC, and if she satisfies all of the inclusion criteria and none of the exclusion criteria, provisional written informed consent will be obtained. The participants will then be interviewed using the HADS through their mobile phone by a rater located in Kyoto University. If the nurse does not satisfy the HADS exclusion criterion, formal written informed consent will be obtained.

The participants will be randomly allocated to one of the four intervention arms via the EDC using a minimization method. Minimization is an adaptive stratified allocation system that is used in clinical trials [24]. Minimization can reduce the imbalance between the numbers of patients in each treatment group over possible confounding factors. The participant’s place of work, total score on the HADS of 11 or higher [22], and whether they have been working as a nurse for one year or more will be used as stratification variables (Figure 1).

**Figure 1 Fig1:**
[figure not shown]
**Flowchart of the trial.** EDC, electronic data capturing.

### Interventions

#### Psychological interventions

In the present factorial-design RCT, the effects of two forms of psychological intervention will be compared: mindfulness-based stress management program and a psychoeducation leaflet.

The stress management program has been developed combining mindfulness-based self-regulation of attention [25] and the cognitive behavioral model of depression adapted from a previously established manual [26]. Although a previous trial of 41 nursing students [27] employed mindfulness meditation with the non-judgmental awareness of moment-to-moment experiences as the central axis [28], we extracted the treatment components of body scan and breathing meditation from mindfulness meditation because these techniques are considered easy to learn and helpful for nurses, in our experience. The stress management program consists of four weekly 30-minute individual sessions and is highly structured, with a detailed manual. The contents of each session are as follows: 1) understanding the cognitive behavioral model of stress and emotion of the participant, 2) reviewing the model and conducting body scanning and breathing exercises, 3) reviewing the results of model and body scanning and then promoting awareness of the cognition of the participant and 4) reviewing the model, providing suggestions about increasing pleasant behaviors and planning a strategy to manage future stress. The feasibility of the program has been examined by employing five nurses as participants in a pilot run, the protocol of which was approved by the institutional review boards of the National Center of Neurology and Psychiatry on 15 November 2013 (approval number: A2013-102). No dropouts due to the program were observed. All the participants reported that the program might be helpful for nurses to manage stress from their work. Some rewordings have been done to the program according to comments from the participants.

The stress management program will be conducted by senior nurses in four individual sessions within the first three months. Senior nurses will have taken a seven-hour workshop, including lectures and role-playing sessions. The detailed manual and videos, including lectures, will be provided to the senior nurses. The senior nurses will be supervised monthly by email once the program commences. All sessions will be audiotaped and 20% of them will be randomly selected and evaluated by two independent researchers to assess the integrity of the program. They will check for adherence to the treatment manual with a checklist for each session.

A leaflet has been prepared for the psychoeducation leaflet groups. This is based on a freely distributed psychoeducation leaflet about healthy mental state written by the Japanese Ministry of Health, Labor and Welfare [29]. The leaflet includes information about checking for signs of stress, relaxation and sleep hygiene, and suggestions for stress management such as exercise, laughter and meeting intimate friends. It also includes a list of consultants for mental health. We have adapted this leaflet to be applicable to our study by adding advice from senior nurses about working without stress. Participants allocated to the leaflet groups will be instructed to read this often, especially when they feel anxious or stressed.

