### Sample size

The sample size was based on a power analysis conducted for the HADS scores. There are no previous reports associated with the stress management program, in terms of nurse-to-nurse interventions, that can contribute to the power calculation of our trial. Based on trials that have used nurses as therapists and the HADS as the primary outcome, one trial has examined the efficacy of cognitive behavioral therapy conducted by nurses for depression in the elderly after lumber fracture operations, and a difference of 3.7 was found compared with treatment as usual [64]. To the best of our knowledge, there have been no reports assessing treatment with omega-3 fatty acids for depression or anxiety in nurses. One systematic review and meta-analysis has shown that treatment with omega-3, ≥60% EPA and ≤40% DHA led to an effect size of −0.026 (95% CI: −0.200 to 0.148), when compared with a placebo [65]. Therefore, the mean difference in the HADS scores was estimated to be 4 ± 6 (SD) between the stress management program and leaflet groups, and between the omega-3 fatty acids and placebo groups. To detect a significant difference at *P* = 0.05 (two-tailed) with a power of 0.9, it was calculated that 48 patients would be required for each of the arms in both comparisons. Thus, allowing for a 20% dropout rate, 60 participants would need to be recruited per group. In the present factorial-design RCT, 30 participants would be necessary for each of the four groups.

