### Data management and analysis

All of the participants who are randomized at baseline will be included in the primary analyses (intention-to-treat (ITT)). First, a descriptive analysis of the variables at baseline will be performed. We do not plan any statistical tests to detect a difference at baseline among the trial arms because we aim to avoid multiple tests, and the decision to adjust for baseline data in RCTs should not be determined by whether baseline differences are statistically significant [66]. However, when clinically important differences at baseline are noted from a clinician’s point of view, a sensitivity analysis will be performed by adjusting for all such possible confounds.

Second, for the primary outcome and all the continuous outcomes assessed at 26 and 52 weeks, differences among groups will be examined using a mixed-model repeated measures analysis. When missing data exist for categorical variables, which are all negative outcomes, an ITT principal will be applied by assuming that all dropouts did not satisfy the outcomes. However, per protocol analyses, where only data from completers are incorporated, will also be presented according to a recent recommendation [67]. We also plan to calculate a number needed to treat (NNT) with a 95% CI if a statistically significant difference among the groups is observed in dichotomous data.

A *P* value of <0.05 will be set to test the null hypothesis for all analyses. Although we understand that this decision might lead to errors in multiple tests, the present trial is the first of its kind to examine prevention interventions in this type of workplace; therefore, we have considered that avoiding beta errors is preferable over alpha errors. However, 95% CIs will always be presented for differences among groups. We will not perform interim analyses to examine the study hypotheses.

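### The sample size makes no allowance for clustering by delivering senior nurse and the stated model names no term for it, so the program-versus-leaflet standard error would be too small if caseloads exceed one and outcomes vary by deliverer

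*Protocol article*

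**What the plan says.** **Delivery.** Under Psychological interventions: "The stress management program will be conducted by senior nurses in four individual sessions within the first three months". The Abstract (Methods/Design) adds: "These sessions are conducted by nurses with a managerial position". They are trained in a seven-hour workshop, work from a manual and videos, and are supervised monthly by email. Leaflet participants read the material themselves.

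**Size.** Trial design: "A total of 30 participants will be allocated to each arm". In the factorial layout this gives 60 program versus 60 leaflet participants. Sample size assumes a HADS difference of 4 with SD 6 at two-sided 0.05, and continues: "with a power of 0.9, it was calculated that 48 patients would be required for each of the arms in both comparisons". It then says: "allowing for a 20% dropout rate, 60 participants would need to be recruited per group".

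**Analysis.** Data management and analysis says that for continuous outcomes "differences among groups will be examined using a mixed-model repeated measures analysis". It describes no random effects or covariance structure.

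The article does not give the number of senior nurses, how many participants each would see, or an ICC for deliverers.

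**The concern.** When one person delivers an intervention to several participants, their outcomes may be correlated because they share that deliverer. Here this can happen only on the program side, because the leaflet side has no deliverer. The repeated-measures part of a mixed model handles correlation within a participant over time. It does not handle correlation between participants who share a senior nurse, unless a term for the senior nurse is added.

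If such correlation exists and is left out, the standard error of program versus leaflet is understated. The P value and 95% CI for one of the two main comparisons would then be too favorable. Separately, the stated 0.90 power would be optimistic for any analysis that does account for it.

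**Working it through.** **Inputs from the Sample size and Trial design sections:** difference 4, SD 6, two-sided alpha 0.05, power 0.90, dropout 20%, 60 recruited per comparison group (30 + 30).

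**Assumed, because the article does not give them:** caseload m (analyzed participants per senior nurse) and ICC. Total variance is taken as 36 in both groups.

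**1. Reproduce the plan's figure.** With independent participants,

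n = 2 × 36 × (1.96 + 1.2816)² / 4² = 72 × 10.507 / 16 = 47.3, rounded up to 48.

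48 / 0.80 = 60. Both match the article, so the calculation contains no design effect. Power at n = 48 is 0.904.

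**2. Add clustering in the program group only.**

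- Design effect in the program group: DE = 1 + (m − 1) × ICC
- Variance of the difference: 36 × (1/48 + DE/48)
- True SE divided by independence SE: r = √((1 + DE)/2)
- Independence SE: 6 × √(2/48) = 1.225
- Type I error if the term is omitted: 2 × [1 − Φ(1.96/r)]
- Power if the term is omitted: Φ[(4 − 1.96 × 1.225)/(1.225 r)]
- Power of a correctly sized test: Φ[4/(1.225 r) − 1.96]
- n per group for 0.90 power with the correct SE: 36 × (1 + DE) × (1.96 + 1.2816)² / 16

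Example, m = 10 and ICC 0.05: DE = 1.45 and r = √1.225 = 1.107. Type I error is 2 × [1 − Φ(1.771)] = 0.077. Correctly sized power is Φ(4/1.356 − 1.96) = Φ(0.991) = 0.839. The required n is 36 × 2.45 × 10.507 / 16 = 57.9, so 58.

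| m | ICC | DE | r | Type I, term omitted | Power, term omitted | Power, correct SE | n per group (recruited) |
|---|---|---|---|---|---|---|---|
| 1, or any m with ICC 0 | – | 1.00 | 1.000 | 0.050 | 0.904 | 0.904 | 48 (60) |
| 2 | 0.02 | 1.02 | 1.005 | 0.051 | 0.903 | 0.901 | 48 (60) |
| 3 | 0.02 | 1.04 | 1.010 | 0.052 | 0.902 | 0.899 | 49 (62) |
| 5 | 0.02 | 1.08 | 1.020 | 0.055 | 0.900 | 0.893 | 50 (63) |
| 10 | 0.05 | 1.45 | 1.107 | 0.077 | 0.881 | 0.839 | 58 (73) |
| 10 | 0.10 | 1.90 | 1.204 | 0.104 | 0.861 | 0.774 | 69 (87) |

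The two power columns describe different tests. The inflated type I error goes with the first. The second is what remains once the test is correctly sized.

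All figures use the normal approximation. At m = 10 there would be only about 48/10 ≈ 5 deliverers, so small-sample degrees of freedom would lower the last power column further.

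**The case against.** The strongest objection concerns what the document actually commits to. A reader might infer that the plan treats participants as independent. It does not say so: a mixed model can carry a senior-nurse effect, and random-effect details are often left to a full protocol or SAP, which is not shown. This stands. The analysis section can be faulted only for naming no such term, not for excluding one. The sample size is different, because it is fixed in this article and reproduces only without a design effect.

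Second, it is an inference that each senior nurse treats several participants. That also stands, although the inference is reasonable. A caseload of one would need 60 trained managerial nurses across four hospitals. Monthly supervision over an entry period from June 2014 to March 2015 also fits successive participants better than a single four-session course per nurse.

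Third, several features should keep the ICC low: a tightly structured manual, four short sessions, videos, audiotaping with adherence checks on 20% of sessions, and a blinded off-site rating at week 26. Place of work is also a minimization factor, which helps balance hospital-level differences. These points favor the smaller values in the table. They do not make the ICC zero, and balancing hospitals does not remove differences between deliverers within a hospital.

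Finally, a reader might infer that the deliverer's identity goes unrecorded, or that one or two good deliverers could carry the result. The article supports neither. Table 1 lists no deliverer ID, but it is an assessment schedule, and all sessions are audiotaped.

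**Conclusion.** The point holds in conditional form. The design is partially nested, the sample size makes no allowance for that, and the stated model names no term for it. If senior nurses have caseloads above one and outcomes vary by deliverer, the standard error for program versus leaflet would be too small.

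The size is unknown. It is negligible at m of 2 to 3 with ICC 0.02 and small at m = 5 with ICC 0.02. It becomes material at m of about 10 with ICC 0.05 or more. The document does not support saying outright that the interval is too narrow, because both m and ICC are assumed.

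Nor should type I error of 0.104 and power of 0.77 be read together as properties of one planned test. At m = 10 and ICC 0.10, the test without the term has type I error 0.104 and power about 0.86. The 0.77 belongs to the correctly sized test.

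The omega-3 comparison is little affected, because capsule allocation is crossed with the program.

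**What to change.** 1. State the number of senior nurses and the expected caseload, and make sure the delivering nurse's ID is in the analysis data for every program participant.
2. For program versus leaflet, prespecify a random senior-nurse effect that applies in the program arms only, with small-sample degrees of freedom, at least as a sensitivity analysis. Report the estimated variance between senior nurses.
3. Add a sentence to Sample size saying that the 0.90 power assumes no clustering by deliverer.

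The cost is one identifier, one model term and one sentence. The confidence interval for the program effect would usually be somewhat wider, and with few deliverers the variance component would be imprecise. No change is needed for the omega-3 comparison.
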